#### Cross-sectional analysis

Mixed linear models: Associations of continuous health and PA outcomes with personal characteristics (eg, sex, SES) will be assessed postintervention, that is, from data collected after the conclusion of the trial. It will be adjusted for the type of school (ie, intervention vs control) and potential clustering within schools and classes, respective random intercepts will be used.

Mixed logistic regression: For categorical outcome measures, after suitable dichotomisation of polytomous outcomes, associations with the same predictor variables as for the mixed linear models will be analysed post-intervention using the same random intercepts.

### Longitudinal analysis

Mixed linear regression: Associations between longitudinal changes in continuous variables (eg, BMI) and individual characteristics, like sex and SES, will be assessed with random intercepts for schools and classes. Longitudinal changes in these outcomes will also be compared between the previous intervention and control schools after adjustment for personal characteristics. Moreover, changes in health parameters will be regressed against changes in PA and nutritional parameters. All analyses will be conducted, with and without adjustment, for the postintervention values of the respective outcomes. Also, potential associations between adjusted school-specific means of longitudinal changes in health parameters and the retrospectively assessed degrees of implementation of intervention measures in the respective schools will be assessed.

Mixed logistic regression: Longitudinal changes in categorical outcomes will be analysed by dichotomising polytomous outcomes. Analyses will be stratified according to the postintervention value of the dichotomised outcome, using mixed logistic regression models of the follow-up outcome with the same random effects structure and the same predictor variables, as previously described, for the mixed linear models. Additional analyses will be conducted by treating the postintervention and the two consequent FU outcomes as repeated measures.

To adjust for biases associated with missing data and/or lost to follow-up, inverse probability weighting will be used. Data imputation will be considered as an additional option if the drop-out rate is moderate (ie, <20%).

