## Methods

### Research setting

This study is conducted in the eight schools originally selected for the *KaziBantu* RCT.^30^ These are quintile three primary schools in the townships and Northern areas of NMB, in the Eastern Cape province of South Africa. The quintiles of South African schools are determined through the national poverty table and are ranged on a scale from 1 (poorest) to 5 (least poor). Quintile three schools represent no-fee paying schools and their communities are adversely affected by poverty and high unemployment rates.

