### Study population

Originally, in the *KaziBantu* project, both *KaziKidz* and *KaziHealth* interventions were conducted in four schools, whereas the other four participating schools were used as controls.^30^ In total, 975 children from fourth to sixth grade (aged 8–16 years) were enrolled in the study; 482 children were allocated to the intervention and 493 to the control arm. At the same time, 160 educators were enrolled among all participating schools; of those, 85 took part in *KaziHealth,* whereas 75 served as waiting-list controls.

This study will follow up children and educators from the *KaziBantu* trial. While all educators who took part in *KaziHealth* have been invited to participate in this follow-up phase, a cohort of children from the *KaziKidz* intervention, who have been identified as having an increased risk for NCDs, have been included in this study. We have defined increased risk as a child presenting at least one of the following cardiometabolic risk factors: (1) overweight or obesity, (2) elevated blood pressure or hypertension, (3) pre-diabetes or diabetes, (4) borderline or dyslipidaemia; according to age appropriate, standard classifications (table 1) and based on *KaziBantu* baseline data from July 2019. Of the 975 children who participated in *KaziKidz*, 544 were classified as «high risk» according to the above-mentioned definition. Since then, 183 children have graduated from primary school resulting in 361 eligible learners. Of those, 240 have consented to participate and have been enrolled in this follow-up study at the time this protocol was published. Of the 160 educators enrolled in the *KaziHealth* program in 2019, 105 have consented to participate and have been enrolled in this study so far.

**Table 1 T1:** Classification criteria for cardiometabolic risk in children

Risk factor	Indicators and cut-off points
Adiposity^59 60^	BMI-for-age (SD)
Overweight	>+1 and ≤+2
Obesity	>+2
Blood pressure^61 62^	SBP and/or DBP (percentiles and mm Hg)
Elevated blood pressure	≥90th and <95th or <90th but ≥120/80
Hypertension stage 1	≥95th and ≤99th or ≥130/80
Hypertension stage 2	>99th or ≥140/90
Glycaemia^63^	HbA1c (mmol/mol)
Pre-diabetes	>39 and <48
Diabetes	≥48
Dyslipidaemia^64 65^	TC (mmol/l)
Borderline	≥4.40 and 5.15
Dyslipidaemia	≥5.15

BMI, body mass index; DBP, diastolic blood pressure; HbA1c, glycated haemoglobin; SBP, systolic blood pressure; TC, total cholesterol.

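### The comparison of change between former intervention and control schools rests on eight schools, and the mixed models named for it come with no small-sample method

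*Protocol article*

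**What the plan says.** Research setting: "This study is conducted in the eight schools originally selected for the" parent trial. Study population gives the split: "interventions were conducted in four schools, whereas the other four participating schools were used as controls".

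Longitudinal analysis, mixed linear regression: associations of change with sex, socioeconomic status and the like "will be assessed with random intercepts for schools and classes". That sentence concerns person-level predictors. The sentence after it, under the same label, compares change between the former intervention and control schools, adjusted for personal characteristics. This is the comparison at issue. For dichotomised outcomes the section plans "mixed logistic regression models of the follow-up outcome with the same random effects structure" and the same predictors.

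Cross-sectional analysis also mentions "potential clustering within schools and classes, respective random intercepts will be used", but there school type is only an adjustment variable and no arm test is planned.

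Data management names Stata 15.1. The article states neither ML nor REML, no reference distribution or degrees-of-freedom method, no significance level and no intraclass correlation.

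**The concern.** School type is constant within a school. Measuring more children sharpens each school's mean but does not add schools, so the uncertainty of the arm effect has to be judged from the spread of four means in each group. A mixed model tested against a normal reference treats the school variance as known, although it is estimated from only 6 degrees of freedom. ML also divides the between-school sum of squares by 8 instead of 6.

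The result is intervals that are too narrow and chance differences between a few schools read as lasting programme effects. The comparison bears on the first objective, long-term effectiveness, and the article intends its findings to inform policy. The mixed logistic model needs particular care, because its usual Wald test is normal-based.

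**Working it through.** The plan gives no error rate, power or ICC, so there is no figure of its own to reproduce.

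**Inputs from the protocol article**
- Eight schools, four per former arm: 8 − 2 = 6 between-school degrees of freedom.
- Children: "240 have consented to participate and have been enrolled in this follow-up study", so 240/8 = 30 per school. The upper limit is 361 eligible, about 45 per school.
- Educators: 105 enrolled so far, about 13 per school.

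**Assumptions**
- Two-sided 5% level.
- School ICC from 0 to 0.20; class ICC 0 or 0.03.
- Equal school sizes, three classes per school (or no class level), no weighting.

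**Limits when between-school variance dominates**
- With REML, the estimated difference divided by its standard error follows t on 6 df. Against 1.96: P(|t6| > 1.96) = 9.8%, or 2.0 times nominal.
- With ML, the standard error is smaller by √(6/8) = 0.866. The effective cut-off is 1.96 × 0.866 = 1.70, and P(|t6| > 1.70) = 14.1%, or 2.8 times nominal.
- The t critical value on 6 df is 2.447, and 2.447/1.960 = 1.25.

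**Simulation, linear model, 240 children** (200,000 balanced data sets per setting, variance estimates held at or above zero; ranges cover the class assumptions)

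| School ICC | REML, normal | ML, normal | REML, t on 6 df |
|---|---|---|---|
| 0 | 3.6-4.4% | 4.3-5.6% | 0.9-1.4% |
| 0.01 | 5.1-5.7% | 6.5-7.4% | 1.7-2.0% |
| 0.02 | 6.5-6.8% | 8.5-8.9% | 2.5-2.7% |
| 0.05 | 8.3-8.6% | 11.5-11.8% | 3.7-4.0% |
| 0.10 | 9.3-9.5% | 13.1-13.5% | 4.5-4.7% |
| 0.20 | 9.6-9.8% | 13.8-14.0% | 4.9-5.0% |

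With 361 children at ICC 0.05, the rates are 8.7-9.2% (REML) and 12.2-12.8% (ML). With 105 educators they are 5.6% and 7.0% at ICC 0.02, 7.1% and 9.3% at 0.05, and 8.6% and 11.7% at 0.10.

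**Simulation, mixed logistic model with Wald z** (school intercept only, 30 children per school, outcome prevalence about 30%, 1,200 data sets per setting): about 4.8% at ICC 0, 6.4% at 0.01, 9.3% at 0.05 and 12.4% at 0.10. The simulation standard error is roughly 1 percentage point at the upper end.

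**Limits of the check.** Unequal school sizes and the planned inverse probability weighting were not modelled. The planned logistic models are stratified by the postintervention value, so each would have fewer children per school than was simulated.

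**The case against.** The strongest reply is that the article never commits to a large-sample test. Estimation method and degrees of freedom are commonly left to an analysis plan, and silence on them in a condensed article is not an error. That stands: the normal reference is an inference. What remains is that the article fixes a model class, including mixed logistic regression, for a contrast with 6 degrees of freedom, and a specific and nearly free alternative is better.

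It is also fair that the study is observational, that the arm comparison is one of several, and that the inflation depends on an ICC nobody has stated. At ICC 0.01 it is slight, and at ICC 0 without class effects there is none.

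Three stronger readings might be inferred and are not supported:
- **That the implementation analysis is inflated too.** The article plans to examine "potential associations between adjusted school-specific means of longitudinal changes in health parameters and the retrospectively assessed degrees of implementation", which is already an analysis of eight school values. Tested with t on 6 df it is not inflated for this reason. Its limit is precision: significance needs |r| above 2.447/√(2.447² + 6) = 0.71.
- **That the repeated-measures models omit a participant term.** The phrase about the same random-effects structure belongs to the stratified logistic models of the follow-up outcome. The repeated-measures sentence comes afterwards and states no structure.
- **That false positives are simply doubled or tripled.** Factors of 2.0 (REML) and 2.8 (ML) are upper limits.

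**Conclusion.** The point holds for one analysis: the comparison of change between former intervention and control schools, by mixed linear and mixed logistic models, on four schools against four. If it is tested against a normal reference with 240 children, a nominal 5% test rejects in about 7-9.5% (REML) or 9-13.5% (ML) of null cases over an assumed school ICC of 0.02 to 0.10. The mixed logistic Wald test reaches about 9% at ICC 0.05 and 12% at 0.10. For the smaller educator sample the linear-model rates are lower.

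These figures depend on the assumed ICC, the estimator, balanced schools and the normal reference, none of which the article settles. Tests of person-level predictors such as sex or socioeconomic status are much less affected. Because the ICC is not known in advance, a test that is valid across its range should be fixed beforehand.

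**What to change.** For the former-arm comparison only, add to the longitudinal analysis:
- **Continuous outcomes:** fit the linear mixed model by REML, with Kenward-Roger or Satterthwaite degrees of freedom for the school-type effect. Confirm that this can be combined with the planned inverse probability weights in the named software. If it cannot, compare covariate-adjusted school means by t on 6 df.
- **Binary outcomes:** compare covariate-adjusted school-level summaries by t on 6 df, or use a permutation test over the school allocation. If that allocation was unrestricted there are C(8,4) = 70 arrangements, and the smallest two-sided p-value is 2/70 = 0.029. If it was restricted, permute only within the scheme used.

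The cost is wording and a software option; no new data are needed. Intervals for the arm effect become about 25% wider than REML with a normal reference. Relative to ML they become up to about 44% wider in the limiting case (1.25 × √(8/6) = 1.44). REML with t on 6 df is conservative when the ICC is very low: 1.7-2.7% at ICC 0.01-0.02. A plain t-test on school means keeps 5% with balanced, normally distributed data.

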### Objectives

The goal of this follow-up study is to determine the long-term post-RCT effectiveness, adoption and continuity of both *KaziKidz* and *KaziHealth* school-based health interventions in disadvantaged primary schools in NMB, South Africa, under real-world conditions and amid the COVID-19 pandemic. To achieve this goal, the following objectives are set:

To assess the effectiveness of the interventions in promoting long-lasting, positive lifestyle changes among children and educators, thereby reducing risk factors for NCDs;To evaluate the postintervention sustainability concerning the continuation of the programme implementation in the schools as well as the institutionalisation within the Eastern Cape Department of Education (ECDoE) in South Africa.To provide recommendations towards guidelines for a health promotion framework, as well as its adaption to new contexts that may be translated into policy and practice.

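### The comparison of former intervention and control schools is adjusted for and stratified by the end-of-trial value, so it measures maintenance since the trial and not the long-term effectiveness in objective 1

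*Protocol article*

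**What the plan says.** The Objectives section sets the goal as to "determine the long-term post-RCT effectiveness, adoption and continuity of both" programmes. Its first objective is "To assess the effectiveness of the interventions in promoting long-lasting, positive lifestyle changes among children and educators".

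The Longitudinal analysis section then fixes the models:

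- Arm contrast for continuous outcomes: "Longitudinal changes in these outcomes will also be compared between the previous intervention and control schools after adjustment for personal characteristics".
- Covariate: "All analyses will be conducted, with and without adjustment, for the postintervention values of the respective outcomes".
- Categorical outcomes: "Analyses will be stratified according to the postintervention value of the dichotomised outcome".
- Supplement: "Additional analyses will be conducted by treating the postintervention and the two consequent FU outcomes as repeated measures".

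The last item lists the post-intervention value separately from the two follow-ups (April and September 2021), so in this section it means the measurement at the end of the RCT. The Cross-sectional analysis section uses the same word more loosely ("postintervention, that is, from data collected after the conclusion of the trial"). The 2019 baseline appears under Study population as the criterion for selecting high-risk children. No longitudinal model names it.

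**The concern.** Objective 1 is a question about the effect of the programmes. The natural contrast is the difference between the original arms at follow-up, with adjustment only for values that the programmes could not have affected. The plan takes its covariate and strata from a value that may already carry the programme effect. It very probably takes the start point of change from there too, since no other reference is named.

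If the RCT shifted that value, change from it captures only later gain or loss, and adjusting for it or stratifying by it removes part of the effect being sought. A real and lasting benefit could then be reported as absent, or a partly lasting one as harm, in a study meant to inform policy.

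**Working it through.** **Inputs.** The article gives no effect size, correlation or power figure, so there is no stated figure to reproduce. The values below are assumptions, shown over a range:

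- D, arm difference at the end of the RCT: −0.30 SD (lower is better).
- f, share of D still present at follow-up: 1, 0.75, 0.5 or 0.
- b, within-arm slope of follow-up on the post-intervention value: 0.5, 0.7 or 0.9.

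**Formulas.** The arm difference is D at the end of the trial and fD at follow-up.

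- Long-term effect: fD.
- Unadjusted change from post-intervention: fD − D = (f−1)D.
- Change adjusted for the post-intervention value: fD − bD = (f−b)D.

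**Continuous outcomes (SD units; positive means apparent harm).**

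| f | Long-term effect fD | Unadjusted (f−1)D | Adjusted, b=0.5 | b=0.7 | b=0.9 |
|---|---|---|---|---|---|
| 1 | −0.30 | 0.00 | −0.15 | −0.09 | −0.03 |
| 0.75 | −0.225 | +0.075 | −0.075 | −0.015 | +0.045 |
| 0.5 | −0.15 | +0.15 | 0.00 | +0.06 | +0.12 |
| 0 | 0.00 | +0.30 | +0.15 | +0.21 | +0.27 |

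At f=1 the adjusted contrast is (1−b)D, so the proportion lost equals b: 50–90% over this range. The adjusted contrast turns to harm only when f<b. A simulation of 400,000 unclustered participants, with equal correlations of 0.5, 0.7 and 0.9 between the three time points, reproduced the table to within 0.005. Adjusting for the pre-intervention value instead recovered fD at every correlation (about −0.30, −0.22, −0.15 and 0.00).

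**Effect of selecting high-risk children.** Selection on a high baseline lowers b. In a simulated cohort restricted to the top 20% on the baseline of that same outcome, a correlation of 0.7 gave b of about 0.51. The adjusted contrast was then (1−0.51)(−0.30) ≈ −0.15 at f=1 and about 0.00 at f=0.5. The unadjusted contrasts were unchanged. The real selection was on any of four risk factors, so the strength of this effect for a given outcome is unknown.

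**Binary outcomes (unselected simulation, cut at +1 SD, correlations 0.5 to 0.9).**

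| f | Marginal OR | OR, condition absent post-intervention | OR, condition present post-intervention |
|---|---|---|---|
| 1 | 0.57 | 0.61–0.66 | 0.73–0.79 |
| 0.5 | 0.76 | 0.84–1.10 | 0.96–1.32 |
| 0 | 1.0 | 1.14–1.70 | 1.25–2.32 |

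Stratification attenuates a maintained effect without abolishing it. If nothing is retained, it produces apparent harm.

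**Repeated measures.** This model has the post-intervention value as an outcome, so it does not condition on it. A single arm effect over one post-intervention and one follow-up value is (1+f)D/2: −0.30 at f=1 and −0.225 at f=0.5. With both follow-ups weighted equally it is (1+2f)D/3: −0.30 and −0.20. At f=0.5 the long-term effect is −0.15, so the model mixes in the end-of-trial difference.

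**The case against.** Much can be said for the plan.

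- *Maintenance is a stated aim.* Study design says the 2021 visits are to evaluate it. Change since the end of the trial is the right quantity for that, and a zero arm difference in change then means the effect was kept. This stands. The fault is only the mismatch with objective 1.
- *The start point of change is never stated.* This also stands. It is a strong inference from the only reference value named, and a fuller document may define it. The adjustment and the stratification, however, are express.
- *No RCT effect is reported.* If D=0 there is no distortion. That is correct, but the plan has to work when D is not zero.
- *Not every analysis conditions on the end-of-trial value.* Linear models are run both ways, the repeated-measures model does not condition, and the cross-sectional models include school type. These are real mitigations, but no planned longitudinal contrast is referenced to the 2019 baseline.
- *After 2019 all eight schools could run the programmes,* and Study design says that no control group is followed and that non-implementing schools serve as comparison. For implementation after the RCT, the end-of-trial value does precede exposure and is a proper baseline. The criticism therefore does not reach the implementation analysis, nor the associations with sex, SES, physical activity and nutrition. It does reach the former-arm comparison, which the Longitudinal analysis section specifies all the same.

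A reader might go further and infer that every planned model shows a lasting benefit as zero or harm. The documents do not support that: zero and harm follow exactly only for the unadjusted change score.

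**Conclusion.** The point holds for the comparison of former intervention and control schools, and for that alone. Its covariate and strata, and by strong inference its starting point, lie after randomised exposure. The resulting contrasts estimate maintenance or decay, not the long-term effect fD. With an assumed D of −0.30 SD, a fully kept effect reads 0.00 on unadjusted change and −0.15 to −0.03 after adjustment (b 0.5–0.9). A half-kept effect (−0.15) reads +0.15 and 0.00 to +0.12. D, f, b and the cut-off are assumptions, and the simulations ignore clustering.

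Two further inferences should be resisted. The documents do not show that the RCT changed the post-intervention values. Nor do they establish that a pre-exposure baseline exists for every outcome and for educators: Study population documents it only through the children's cardiometabolic criteria and dates it July 2019, while the Introduction places the RCT between January and October 2019.

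**What to change.** 1. State the start point of change in the Longitudinal analysis section.
2. For the effectiveness question, compare the original arms at April and September 2021, adjusting for the 2019 baseline value of the outcome and keeping the planned school and class random intercepts. A repeated-measures model that includes baseline with arm-by-time terms is an alternative.
3. For binary outcomes, use baseline status as a covariate in the arm comparison in place of post-intervention strata.
4. Apply items 2 and 3 wherever a baseline is held and confirmed to precede exposure. Reconcile the July 2019 date with the January to October 2019 trial period, and say which outcomes and which group (children, educators) have such a baseline.
5. Keep the post-intervention-adjusted and stratified arm contrasts as secondary analyses, labelled as maintenance since the end of the RCT.
6. Note that control schools could adopt the programmes after 2019, so the contrast compares the original allocation under open uptake.

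The other planned associations need not change. The cost is revised wording, some extra analysis and a check of baseline availability. The residual SD may be slightly larger because the baseline is older than the post-intervention value.

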### Intervention

The *KaziKidz* intervention consists of a tailored, ready-made teaching material toolkit for grades 1–7 and addresses children’s risk factors for NCDs, health behaviours and psychosocial health. On the other hand, *KaziHealth* is designed as a workplace intervention targeting educators’ health and well-being through health risk assessments and personalised lifestyle coaching. The interventions have been described in detail elsewhere^30^ and all teaching materials and other project resources are freely available online.^37^

After conclusion of the *KaziBantu* RCT in 2019, all eight schools were given the freedom to conduct *KaziKidz* and *KaziHealth*. Thus, all children from grades 1–7 may have participated in *KaziKidz*, regardless of health condition. However, the implementation of *KaziKidz* and *KaziHealth* has proceeded independently and without support from the project team in all schools, under so-called «real-world» conditions. Therefore, the delivery of the programmes might have been only partially implemented. For instance, some schools might have needed to adapt *KaziKidz* to comply with COVID-19-related requirements, while other schools might have not been able to, or decided not to, continue with the intervention at all.

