### Study design

This study represents an observational follow-up of the *KaziBantu* RCT and has been designed as a longitudinal study to investigate the long-term effects of both lifestyle interventions, *KaziKidz* and *KaziHealth*, on health parameters and behaviours of a cohort of high-risk children, as well as all educators originally included in the RCT. The overall effectiveness and sustainability of the programmes will be assessed using a mixed-methods approach, including quantitative and qualitative data collection methods and analyses (figure 1). Recruitment has started in March 2021. Assessments of health outcomes will be performed both for children and educators at two time points: April 2021 and September 2021, that is, 1.5 and 2 years post-RCT, to evaluate the maintenance of healthy, active lifestyles and its effect on an individual level. As part of the postintervention evaluation, the extent of *KaziKidz*’s implementation in the schools will be obtained from school representatives at both time points to be able to correlate the observed outcomes with continued participation in the original intervention. A qualitative analysis of the school headmasters’ experiences with *KaziKidz,* as well as of its incorporation into the schools’ curriculum with officials from the ECDoE, will take place 2 years post-RCT, in October 2021. Additionally, qualitative analyses will also be conducted with school educators on their experiences with, and incorporation of, *KaziHealth* into their lifestyles 2 years post-RCT, in October 2021. Further information on the adoption and acceptance of *KaziKidz* by educators and parents, and of *KaziHealth* by school headmasters’ and ECDoE officials will be obtained during October 2021.

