### Impact analysis

For the second objective of assessing the overall community impact of the intervention, its acceptability, adoption, implementation and maintenance will be explored at the individual, community and organisational level. For this purpose, a systematic analysis will be performed based on the RE-AIM evaluation framework and its proposed dimensions ((1) Reach, (2) Efficacy, (3) Adoption, (4) Implementation and (5) Maintenance).^50^ Each dimension will be analysed separately, using pieces of data collected by the above-mentioned methods and as described in table 2, and results will be expressed as percentages. Ultimately, the combination of all five dimensions will result in a score that Glasgow and colleagues refer to as «public health impact» or «population-based effect».^50^

**Table 2 T2:** Impact analysis evaluation based on the RE-AIM framework

Dimensions	Social level	Evaluation criteria
Reach Proportion of the target population that has participated in the intervention	Individual: Children Educators	Number and characteristics of children who: Have received at least half the planned lessons, as reported by the educators. Number and characteristics of educators who: Have received the health risk assessment. Have attended at least one face-to-face coaching session.
Efficacy Success rate of the intervention in reducing risk factors	Individual: Children Educators	Changes in: Anthropometric measurements. Clinical parameters. Quality of life.
Adoption Proportion of settings that has incorporated the intervention	Organisational: School educators School principals	Number and characteristics of: Schools that implemented the intervention. Health-promoting activities per school.
	Community: School educators Parents	Number and characteristics of: Educators who have adopted *KaziHealth* recommendations. Parents aware of and supporting *KaziKidz* activities.
Implementation Extent to which the intervention has been embedded in the schools under naturalistic conditions	Organisational: School principals	Number of: Grades and classes participating in the intervention. Terms per school year in which the intervention is being taught. Staff involved in delivering the intervention.
Maintenance Adherence to and dissemination of the intervention	Individual: Children Educators	Changes in: Physical activity and dietary behaviour.

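### The implementation–outcome analysis gives each school one degree of KaziKidz implementation, which nothing ties to the grades the followed children attended

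*Protocol article*

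**What the plan says.** All places are in the protocol article.

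- **Purpose.** Under Study design, school representatives report the extent of KaziKidz implementation at both 2021 time points, "to be able to correlate the observed outcomes with continued participation in the original intervention".
- **Analysis.** Under Longitudinal analysis, the association is between "adjusted school-specific means of longitudinal changes in health parameters and the retrospectively assessed degrees of implementation of intervention measures in the respective schools". Both sides are school-level quantities.
- **Who could be taught.** Under Intervention, after the trial "all children from grades 1–7 may have participated in" KaziKidz. Schools acted without project support, and partial delivery is expected.
- **Who is followed.** Under Study population, "975 children from fourth to sixth grade (aged 8–16 years) were enrolled in the study"; of these, "544 were classified as «high risk» according to the above-mentioned definition"; and "Since then, 183 children have graduated from primary school resulting in 361 eligible learners".
- **What is recorded.** In Table 2, Implementation is an organisational count that includes "Grades and classes participating in the intervention", together with terms and staff. Under Reach, the same table lists children who received at least half of the lessons, as reported by educators. The article does not connect that measure to the outcome models.

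**The concern.** The cohort occupies a narrow band of grades, whereas the programme could be taught in any of seven. A single value per school describes the cohort's exposure well only if delivery was much the same across grades. A school that kept the programme going in the lower grades would count as an implementer although none of the followed children was taught. A school that kept it only in the upper grades could score low although the followed children were taught.

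The Discussion presents the link between integration in the schools and health effects as a main product of the study. Error in the exposure would usually pull that association towards zero, and a null result could then be read as evidence that continued delivery makes no difference. With eight schools there is little room for such dilution.

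**Working it through.** **1. Cohort figure.** 544 high-risk − 183 graduated = 361, which is the article's own number of eligible children.

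**2. Where the cohort sits.** Grades 4, 5 and 6 in 2019 become 5, 6 and 7 in 2020 and 6, 7 and 8 in 2021. The share that left is 183/544 = 33.6%, about one grade in three. If the 544 had been spread evenly over three grades (an assumption), losing the oldest would leave 544 × 2/3 = 362.7, against 361 stated. So, apart from repeaters, the cohort was in grades 5–6 in 2020 and 6–7 in 2021. The article does not state this; it is derived.

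**3. Two-school example.** Assume the degree is the share of the seven grades taught.

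| School teaches | Score | Cohort grades taught, 2020 (5–6) | Cohort grades taught, 2021 (6–7) |
|---|---|---|---|
| Grades 1–4 | 4/7 = 57% | 0 of 2 | 0 of 2 |
| Grades 5–7 | 3/7 = 43% | 2 of 2 | 2 of 2 |

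The higher-scoring school gave the cohort nothing. A school teaching only grades 6–7 (2/7 = 29%) would give full exposure in 2021 but only 1 of 2 grades in 2020.

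**4. Range over uneven delivery.** Let ρ be the correlation between grades of one school in whether they are taught. The article gives no value. For a count over k = 7 grades and the cohort's m = 2 grades in one year,

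corr = [m + m(k−1)ρ] / √{[k + k(k−1)ρ][m + m(m−1)ρ]}.

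At ρ = 0 this is 2/√14 = 0.53. At ρ = 0.5 it is 8/√(28 × 3) = 0.87.

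The reversal and tie columns come from a simulation of school pairs in which each grade is taught with average probability one half. They count only pairs with different scores.

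| ρ | corr(score, cohort exposure) | Exposure order reversed | Exposure equal |
|---|---|---|---|
| 0 | 0.53 | 11.8% | 35.6% |
| 0.2 | 0.72 | 7.1% | 31.3% |
| 0.5 | 0.87 | 2.7% | 26.5% |
| 0.8 | 0.96 | 0.5% | 17.3% |
| 1 | 1.00 | none | not simulated |

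**5. Set against eight schools.** The two-sided 5% critical correlation with n = 8 is 0.707. Suppose the outcome depends on delivery only through the cohort's own exposure and a simple correlation is used. The true correlation needed for the attenuated value to average 0.707 is then 0.707/0.724 = 0.98 at ρ = 0.2, 0.707/0.873 = 0.81 at ρ = 0.5 and 0.707/0.959 = 0.74 at ρ = 0.8. At ρ = 0 it would exceed 1 (0.707/0.535 = 1.32), so it cannot be reached.

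**The case against.** **The scoring rule is not given.** A reader might infer that the plan scores the degree over grades 1–7. The article does not say so. That reading joins the toolkit's range to the Implementation row of Table 2, which serves the RE-AIM objective, and the questionnaire items are not shown. They may record individual grades. This stands, and it limits what can be said about size. The stated analysis nevertheless uses one value per school.

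**Participation is not defined as the individual child's.** Study design speaks of implementation in the schools. It would be too strong to say that the plan promises a child-level exposure and then fails to deliver it.

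**Other analyses exist.** A reader might take this as the only link between delivery and health. Study design also names participants from schools that refuse implementation as comparison groups. That comparison is at school level too, so it does not cure the mismatch.

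**Delivery may have been school-wide.** The examples under Intervention are of schools that adapt or stop the programme. Nothing describes delivery confined to low or high grades, so outright reversal of the ranking is a possibility and not something the article shows.

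**A school-level exposure has merit.** It suits educators, and it suits a programme meant to change the school environment. This is a good reason to keep it alongside a cohort-specific score.

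**A within-school contrast is no cure-all.** With about two cohort grades it is largely grade 6 against grade 7 in 2021, mixed with age and teacher. It vanishes if delivery is school-wide.

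**Conclusion.** The point holds in a limited form. The plan fixes one exposure value per school and nothing ties it to the grades the followed children attended, so the exposure can misstate what the cohort received. Under share-of-grades scoring, the correlation between score and cohort exposure in one year runs from 0.53 to 0.96 for ρ from 0 to 0.8. The problem is nil if schools taught all grades or none.

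The conclusion rests on three things: ordinary grade progression with few repeaters, a degree that reflects the whole school, and some unevenness of delivery across grades. Only the first has support in the article's figures; the other two are open. The existing random intercepts for classes do not help, because the exposure still enters at school level. The documents do not support a claim that the schools will be wrongly ranked, nor that moving to classes would yield many independent exposures.

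**What to change.** For the children's outcomes under Longitudinal analysis:

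1. Score KaziKidz implementation for the grades or classes the cohort attended in 2020 and in 2021. Use the educator-reported lesson receipt already planned under Reach and the grades, classes and terms items under Implementation, recorded by grade and not only as a count.
2. Enter this score at class level in the planned mixed model, with the school and class random intercepts and adjustment for grade or age.
3. Keep the school-wide degree for RE-AIM, for educators and as a secondary analysis for children.
4. Report a within-school contrast only if delivery differed between cohort grades or classes. State that it may be confounded by grade and teacher, and that classes within a school are not independent exposures.

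The cost is slightly more detail in the questionnaire and one more analysis. If delivery proves to have been school-wide, the new score agrees with the old one and little is lost.
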